### Control group

Residents in the control group have at least three interviews with the research assistant. Completing the measures and taking part in the interview gives them an opportunity to talk about their feelings. The extent to which they feel that this is therapeutic is explored in the interviews.

**Figure 1 F1:**
[figure not shown]
**Recruitment and follow-up procedure**.

The research assistant collects baseline data from all residents taking part in the study (T1), then opens the next envelope in sequence to ascertain group allocation. Residents in the control group are reminded that they will still have the opportunity to talk to the researcher about how they are feeling and about their views on taking part in the study. Residents in the intervention groups are given the framework of therapy questions (Table 1) so that they have an opportunity to think about their answers before the therapy interview. The research assistant arranges a time for the therapist to conduct the therapy interview (usually within a couple of days). She also leaves a picture of the therapist with the participant information sheet and the date and time of the therapy session (session reminder card) so that the resident is not confused when visited by another person. The therapist arranges a mutually convenient time for the therapy visits. Although these documents can be bequeathed once the participant has died, they can also be given to people of their choosing at any time. If they wish, residents can choose to keep the document for themselves and not bequeath it. Care home managers keep a list of all the residents who have "generativity" documents to ensure they are sent to recipients once the resident has died. The nurse leaves a session reminder card with the resident as a reminder of when the research assistant will call back to arrange the T2 interview (approximately one week later).

At recruitment the research assistant asks residents in the intervention group to nominate a family member or friend who visits them regularly in the care home. With the resident's permission, the nominated family member or friend is invited to take part in a telephone interview once Dignity Therapy has been completed. The nominated family member or friend is often the recipient of the "generativity" document. Residents are not excluded if they do not nominate a family member. Should they wish to do so, they can chose to leave their "generativity" document with their personal effects rather than to a named person. If the resident mentions that they wish to bequeath to someone other than the nominated family member or friend we will seek permission from the resident to also invite them for interview. The research assistant follows up with the care home to determine when the resident has died. We complete interviews three months post bereavement with all nominated family and friends and any additional recipients of the document.

### Outcome measures

Both quantitative and qualitative outcomes are assessed. These are collected from residents by face-to-face interviews at two time-points: approximately one (T2) and eight weeks (T3) after the dignity document has been completed, and the equivalent in the control group. Longer-term follow-up has not been included in the previous evaluation of Dignity Therapy, or in the current trials being conducted by [name] and colleagues. However, we believe it is important to evaluate the longer-term impact of the intervention. The feasibility of doing this is explored as part of this feasibility study. Quantitative measures have been validated and used with older people and are fairly quick and easy to use. Qualitative interview schedules have been developed for the study.

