**Methods/design:**

A randomised controlled open-label trial. Sixty-four residents of care homes for older people are randomly allocated to one of two groups: (i) Intervention (Dignity Therapy offered in addition to any standard care), and (ii) Control group (standard care). Recipients of the "generativity" documents are asked their views on taking part in the study and the therapy. Both quantitative and qualitative outcomes are assessed in face-to-face interviews at baseline and at approximately one and eight weeks after the intervention (equivalent in the control group). The primary outcome is residents' sense of dignity (potential effectiveness) assessed by the Patient Dignity Inventory. Secondary outcomes for residents include depression, hopefulness and quality of life. In view of the relatively small sample size, quantitative analysis is mainly descriptive. The qualitative analysis uses the Framework method.

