### Intervention group

The therapy is delivered by a palliative care nurse who has been trained in Dignity Therapy by [name] (who developed it). Training included the theoretical basis for the intervention, demonstrations of Dignity Therapy, a detailed overview of the manual, editing the Dignity Therapy documents and working with residents to produce a document that will be helpful for them and its recipients.

A standard framework of questions used in the therapy is given to residents in the intervention group (after randomisation) to give them the opportunity to think about their responses before the session (Table 1). The question framework provides a flexible guide for the nurse delivering the therapy (the therapist) to shape the interview, based on patients' level of interest and responses. The therapist follows the residents' cues, helping them to structure and organise their thoughts, for example, by asking questions about time sequences, how events are causally related to each other and facilitating the disclosure of thoughts, feelings and memories. These interviews are tape-recorded, quickly transcribed verbatim then shaped into a narrative using a formatted editing process. This includes clarifications (eliminating colloquialisms, non-starters and sections not related to the "generativity" material, such an interruptions), chronological corrections, tagging and editing any content that might inflict significant harm on recipients of the document (after discussion with the resident) and finding a suitable ending for the document which is appropriate to the residents' overall message. Another session is arranged for the therapist to read the edited transcript to the participants, who are invited to make any editorial suggestions, including identifying errors of omission or commission. Once these "generativity" documents are finalised, they are given to residents to share with anyone they choose. There is no evidence from previous studies that this has been problematic.

**Table 1 T1:** Framework of questions used in Dignity Therapy

• Tell me a little about your life history; particularly the parts that you either remember most, or think are the most important? Another way of putting this, which may elicit answers from some residents, is to ask, when did you feel most alive?
• Are their particular things that you would want your family to know about you, and are their particular things you would want them to remember?

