• What are the most important roles you have played in your life (family roles, vocational roles, community service roles, etc)? Why were they so important to you, and what do you think you accomplished within those roles?

• What are your most important accomplishments, and what do you feel most proud of?

• Are there particular things that you feel still need to be said to your loved ones, or things that you would want to take the time to say once again?

• What are your hopes and dreams for your loved ones?

• What have you learned about life that you would want to pass along to others? What advise or words of guidance would you wish to pass along to your [son, daughter, husband, wife, parents, other(s)]?

• Are their words or perhaps even instructions you would like to offer your family, in order to provide them with comfort or solace?

• In creating this permanent record, are their other things that you would like included?

Since residents' conditions can fluctuate rapidly, the timing of the contacts can be relaxed and meetings rescheduled. If a resident's condition deteriorates, meetings are rescheduled up to three times before sensitively withdrawing them from the study. The therapist makes detailed notes of her experiences of giving each intervention and any deviations from the protocol. One in three therapy transcripts is randomly selected for review by the principal investigators. A quality assurance protocol has been developed to assess adherence to the Dignity Therapy protocol and deviations from the protocol will be reported as part of the feasibility study.

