#### Main outcome for residents

The primary outcome is residents' sense of dignity (potential effectiveness). This will be assessed at baseline (T1) and at one week (T2) and eight weeks (T3) follow-up, using the Patient Dignity Inventory [9]. This measure evolved directly from the dignity model, therefore, questions correspond to each of the model themes and sub-themes, including: physical, psychosocial, existential and spiritual domains of concern or distress. This measure has been validated in Canada and has been shown to have excellent face, internal, test-retest and concurrent validity.

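### T2 and T3 are counted from completion of the dignity document, which only the therapy arm can reach, so comparable timing and full follow-up of both randomised groups are intended but not secured

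*Protocol article*

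**What the plan says.** **Therapy-arm clock.** The protocol article (Outcome measures) places the two follow-up interviews "approximately one (T2) and eight weeks (T3) after the dignity document has been completed, and the equivalent in the control group". The abstract counts from the intervention instead, again with an equivalent for controls. The section on the main outcome names the time points without a starting date: "This will be assessed at baseline (T1) and at one week (T2) and eight weeks (T3) follow-up, using the Patient Dignity Inventory".

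**Steps before the document is complete.** Under Recruitment Procedure, the research assistant collects T1, "then opens the next envelope in sequence to ascertain group allocation", and books a therapy interview, usually a couple of days ahead. Under Intervention group, "These interviews are tape-recorded, quickly transcribed verbatim then shaped into a narrative using a formatted editing process". A further session follows in which the therapist reads the text back and the resident can ask for changes. Because residents' conditions fluctuate, "the timing of the contacts can be relaxed and meetings rescheduled". The article states no upper limit on the whole process.

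**Controls.** The Control group section promises at least three interviews and gives no dates.

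**Residents who do not finish.** Secondary outcomes for residents lists uncompleted interventions among the things to be recorded. Under Intervention group, a resident who deteriorates has meetings rescheduled up to three times and is then withdrawn from the study. The Control group section has no matching sentence.

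**Use of the data.** Quantitative data says the arms will be compared on dignity and the secondary outcomes, with effect sizes reported. Sample size calculations names estimation of an effect size for a later trial as an aim.

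**The concern.** A randomised comparison needs a time zero that every participant has, and that does not depend on what happens after allocation. Completion of the document meets neither condition. It does not exist for controls, and in the therapy arm it comes later for residents whose visits have to be moved because they are unwell.

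Two things are at stake. The first is timing. In a frail population, if one arm is measured systematically later after baseline than the other, any decline over that gap is mixed with the treatment contrast. The second is who is measured. If a resident without a finished document has no assessment date, follow-up in the therapy arm can come to depend on staying well enough to finish, with no corresponding condition for controls.

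Both bear on the between-group effect size that is meant to inform Phase III. Aims and objectives also lists follow-up among the methods being piloted, so an undefined control clock could be carried into the larger trial.

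**Working it through.** **1. The plan's own figure.** Inputs from Sample size calculations: 64 residents, 25% loss, effect size 0.80 SD, two-sided 5%. Equal allocation is inferred from the blocks of two under Randomization.
- Analysed: 64 × 0.75 = 48, or 24 per arm.
- Two-sample t-test power for 0.80 SD with 24 per arm: 77.4%. The stated 77% is reproduced.
- Standard error of the difference, in SD units: √(2/24) = 0.29.

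The point does not rest on the power figure. It supplies the standard error used below.

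**2. Who has a date under the stated rule.**

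| Resident | Event that starts the clock | T2 and T3 date |
|---|---|---|
| Therapy, document finished | Completion | Completion + 1 and + 8 weeks |
| Therapy, deteriorates and meetings fail | None | Withdrawn from the study |
| Therapy, not finished for another reason | None | Not stated |
| Control | None | An equivalent, with no date to count from |

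Only the first row is fully determined. Every row does have a date on which the envelope was opened.

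**3. What the timing gap could be.** The document gives no time from randomisation to completion, so let it be L days (assumed).

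*Case A: controls counted from randomisation.* Therapy T2 falls at L + 7 days against 7, and T3 at L + 56 against 56.

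| L (days, assumed) | T2 therapy vs control | T3 therapy vs control |
|---|---|---|
| 7 | 14 vs 7 | 63 vs 56 |
| 14 | 21 vs 7 | 70 vs 56 |
| 28 | 35 vs 7 | 84 vs 56 |
| 42 | 49 vs 7 | 98 vs 56 |

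*Case B: controls given a typical therapy interval.* The average gap can be near zero. Only the extra spread in the therapy arm remains.

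The text shown does not say which case applies.

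**4. What that could do to the contrast.** All rates here are assumptions, because the document gives none.
- *Drift:* worsening of 0.05 to 0.10 SD per month × a gap of 0.5 to 1.0 month (2 to 4 weeks) = 0.025 to 0.10 SD. With the therapy arm measured later, this works against therapy.
- *Selection:* if a share p of therapy residents is not measured and would have scored d worse, the therapy mean shifts by p × d. With p of 10 to 20% (3 to 6 of 32) and d of 0.5 to 1.0 SD, the shift is 0.10 × 0.5 = 0.05 to 0.20 × 1.0 = 0.20 SD, in favour of therapy.
- *Together:* from 0.05 − 0.10 = −0.05 SD to 0.20 − 0.025 = +0.175 SD. Even the sign is open.
- *Scale:* 0.10/0.29 is about a third of a standard error, and 0.20/0.29 about two thirds.

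**The case against.** The abstract and Outcome measures both say that controls are assessed at the equivalent time, so matching is intended. Figure 1, on recruitment and follow-up, is not available here, and the article condenses a fuller protocol. A rule for control dates may stand in either. The therapy interview is usually within a couple of days and transcription is described as quick, which suggests short delays. The study is a feasibility trial with mainly descriptive analysis, and any assumed bias is less than one standard error. Finally, a fixed interval from randomisation needs an anticipated therapy duration, yet the time taken to deliver therapy is itself a feasibility outcome. A T2 taken before the document would not measure the post-therapy state the authors want.

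Much of this stands, and it rules out three stronger readings that a reader might infer:
- *That the arms are in fact measured at different times.* The text states the opposite intention. It only fails to secure it.
- *That the research assistant picks the control dates at will.* No section says so.
- *That non-completers are dropped, leaving completers against all controls.* No section removes a resident for non-completion alone. Withdrawal is tied to deterioration, and Quantitative data plans to compare drop-out and missing data between the groups.

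What does not fall away is the stated rule. It names a starting event that controls cannot have and some therapy residents never reach. Comparing drop-out between the groups would reveal an imbalance but would not recover the missing outcomes. Descriptive analysis does not remove bias from an effect size that is reported for planning. The objection to a rigid interval is fair and is met by the width of the window.

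**Conclusion.** The concern holds in a limited form. T2 and T3 are anchored to a post-randomisation event specific to the therapy arm, whose timing varies with residents' condition. The control equivalent has no date in the text shown, and therapy residents without a finished document have no T2 or T3 under the rule. Comparable timing and complete follow-up by randomised group are therefore intended but not secured.

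The document does not allow the size of any bias to be derived. The illustrative range of −0.05 to +0.175 SD rests wholly on assumed decline, delay and non-completion, and on controls being counted from randomisation. If controls are given a typical therapy interval, the average drift term can be close to zero. If Figure 1 or the fuller protocol already holds a control rule, what remains is to state it in the text and to deal with non-completers. The point merits a change because the effect size and the follow-up method are both meant to serve Phase III.

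**What to change.** 1. Define T2 and T3 target dates in both arms from the randomisation date, the day the envelope is opened after T1. Use one planned interval for everyone: the anticipated time from randomisation to finished document, plus one week for T2 and plus eight weeks for T3.
2. Apply the same window in both arms, wide enough that most T2 visits follow the document. Say that the anticipated interval is a planning assumption.
3. Seek T2 and T3 from every randomised resident who is willing and able, whether or not the document is finished. Reconcile this with the text on withdrawal from the study, which appears only under Intervention group, so that the document says who is followed up in each arm.
4. Record days since randomisation and days since document for each assessment. Use days since document for secondary description only.
5. Use one description of the starting point in the abstract, Outcome measures, Main outcome for residents and Recruitment Procedure.

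**Cost.** New wording and a booking rule, with no added visits. The interval from document to T2 will vary in the therapy arm, and a few T2 visits may precede a late document. For those residents T2 will not describe the state after completed therapy; the recorded days since document will identify them.

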#### Main outcome for residents

The primary outcome is residents' sense of dignity (potential effectiveness). This will be assessed at baseline (T1) and at one week (T2) and eight weeks (T3) follow-up, using the Patient Dignity Inventory [9]. This measure evolved directly from the dignity model, therefore, questions correspond to each of the model themes and sub-themes, including: physical, psychosocial, existential and spiritual domains of concern or distress. This measure has been validated in Canada and has been shown to have excellent face, internal, test-retest and concurrent validity.

#### Secondary outcomes for residents

*Potential effectiveness *is also assessed using: the Geriatric Depression Scale [11] (psychological distress); the Herth Hope Index [12] (hopefulness); the EQ-5D [13], and a two item measure used by [name] in the current trials of Dignity Therapy (quality of life). With the consent of participants, we are conducting a detailed qualitative analysis of the therapy transcripts to provide insight into concerns which might impact on the effectiveness of the intervention.

To assess *feasibility *of delivering Dignity Therapy in this setting, time taken to organize and conduct the Dignity Therapy sessions, transcribe and edit narratives, deviations from the therapy protocol and uncompleted interventions and the reasons, and the therapist's perceptions of competence as a result of training are recorded.

To assess the *acceptability *of Dignity Therapy we are conducting semi-structured interviews with residents in the intervention group to obtain their views on the intervention. The therapist is recording her experiences of delivering the therapy and her observations of resident's responses during and after the therapy. As suggested by Ferrell [14], we are reporting case studies of any difficult cases.

#### Demographic measures

Demographic information is collected, including: cognitive functioning (using the Blessed Orientation Memory Concentration test, [10]), co-morbidity (using the Comorbidity Index and Scores of Charlson, [15]), performance status (using Karnosfsky scores, [16]) and ability to perform activities of daily living (Barthel scores, [17]), age, gender, ethnic group.

#### Outcome measures for family/friends/recipients of "generativity" documents

In completion of the therapy, semi-structured telephone interviews are conducted with residents' family/friends and other recipients of the "generativity" documents to obtain their perceptions of the impact of the intervention, on themselves and on the resident, and their views on taking part in the study. For residents who die in the data collection period of the study, follow-up telephone interviews are conducted with family/friends/recipients of the "generativity" documents at three months post bereavement. As in the initial interview, these cover their perceptions of the impact of the intervention, on themselves and on the resident, and their views on taking part in the study. They are also asked to complete the Complicated Grief Assessment [18], which is used to screen for complicated grief reactions. The questionnaire is mailed to them after the telephone interview along with a pre-paid envelope in which to return it. Their age, gender, ethnic group and relationship to residents are also recorded.

#### Piloting methods for a Phase III trial

Time taken to obtain informed consent and collect outcomes, exclusions, recruitment and drop-out rates (residents and their family and friends) are recorded. In addition their views on taking part in the study (e.g. being randomised) are sought in qualitative interviews, and their views on completing the outcome measures are recorded when they are completing them. Any problems with completing measures will be reported, including missing data.

### Analyses

#### Quantitative data

In view of the relatively small sample size, analyses will be mainly descriptive. However, between and within participant comparisons of outcomes will be conducted and the appropriate effect size estimates reported. The intervention and control group will be compared on the main outcome (a sense of dignity) and secondary outcomes (depression, hopefulness and quality of life). We will also compare Time 2 and Time 3 follow-up with baseline for both groups on these measures. The two groups will also be compared on demographic characteristics and baseline measures. If necessary these will be controlled for in the analyses. We will also report recruitment rates and compare drop-out rates and missing data in the two groups.

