## Aims and objectives

The aims of the study are to assess the feasibility, acceptability and potential effectiveness of Dignity Therapy to reduce psychological and spiritual distress in older people in care homes. The specific objectives are to:

a) Determine whether Dignity Therapy is likely to increase peoples' sense of dignity or reduce psychological or spiritual distress.

b) Determine whether it is feasible to provide Dignity Therapy to older people in care homes.

c) Determine whether Dignity Therapy is acceptable to residents and their families.

d) Pilot methods for a larger (Phase III) randomized controlled trial (e.g. recruitment, randomization, follow-up, suitability of measures).

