### Sample size calculations

We are obtaining in-depth information on taking part in the study and receiving therapy from a relatively small sample, rather than aiming to detect significant group differences. One of the aims of the study is to estimate the effect size for an RCT. Allowing for a 25% loss at follow-up, a sample of 64 will give us 77% power to detect an effect size of 0.80 standard deviation units in the Dignity Inventory [9] between the intervention and control groups at the (two-tailed test) 5% level of significance. This will be sufficient to estimate recruitment, follow-up rates and the sample size for a Phase III trial, and to explore qualitative outcomes.

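### The effect of Dignity Therapy should be judged on one baseline-adjusted between-arm Patient Dignity Inventory difference at a named time; the planned within-arm comparisons with baseline cannot show it

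*Protocol article*

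**What the plan says.** Objective (a), under Aims and objectives, is to "Determine whether Dignity Therapy is likely to increase peoples' sense of dignity or reduce psychological or spiritual distress". The abstract and the Discussion say the study will show whether the therapy is likely to be effective, and the abstract adds that it will inform whether a Phase III trial is desirable. The sample size section lists estimating the effect size for such a trial among the aims.

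The primary outcome is the Patient Dignity Inventory: "This will be assessed at baseline (T1) and at one week (T2) and eight weeks (T3) follow-up". Neither follow-up time is named as the main one. The power statement refers to a single contrast, "between the intervention and control groups at the (two-tailed test) 5% level of significance", and gives no time.

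Under Analyses, Quantitative data, the two groups are to be compared on the main and secondary outcomes. The protocol then adds: "We will also compare Time 2 and Time 3 follow-up with baseline for both groups on these measures". Demographic and baseline measures are compared between groups and controlled for only where this is found necessary. The same section calls the analyses mainly descriptive, and the sample size section says the study does not aim to detect significant differences.

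**The concern.** Three choices are left open or fixed unhelpfully, and all bear on one question: which number tells the sponsor that the therapy is promising?

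- **Within-arm change stands beside the randomised contrast with no stated role.** A baseline-to-follow-up change in the therapy arm contains whatever would have happened anyway. The protocol itself supplies reasons to expect such change. The Control group section treats completing measures and being interviewed as a chance to talk about feelings, and asks whether residents find this therapeutic. The Intervention group section has residents who deteriorate withdrawn after up to three rescheduled meetings, and the sample size section allows 25% loss, so change is seen only in those who remain.
- **There are two times and no primary one.** The effects at one and eight weeks may differ, and either could be carried forward.
- **Baseline adjustment is conditional.** Whether to adjust is decided after the baseline data have been compared, so the estimator is not fixed. If no imbalance is seen, the precision available from the baseline score may be given up.

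At stake are the conclusion on objective (a) and the effect size used for Phase III. A within-arm effect size carried into planning could mis-size that trial.

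**Working it through.** **1. The protocol's own figure.** Inputs from Sample size calculations: "a sample of 64 will give us 77% power to detect an effect size of 0.80 standard deviation units", two-sided 5%, and "Allowing for a 25% loss at follow-up". Randomisation in blocks of two implies 1:1 allocation.

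- Analysed: 64 × 0.75 = 48, or 24 per arm.
- Two-sample t test: df = 2 × 24 − 2 = 46; noncentrality = 0.80 × √(24/2) = 2.77.
- Power from the noncentral t distribution = 77.4%.

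The stated 77% reproduces. It describes one between-arm comparison.

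**2. What within-arm tests can show when the therapy does nothing.** The documents give no expected change, so this is an illustration. Assume the same true mean change in both arms, expressed in SD of change, and a two-sided 5% paired t test in each arm with n = 24.

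- Power in one arm: p, from the noncentral t with df = 23 and noncentrality = change × √24.
- Exactly one arm significant: 2p(1 − p).
- Therapy arm alone significant: p(1 − p).

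| Equal change in both arms (SD of change) | p | Exactly one arm | Therapy arm alone |
|---|---|---|---|
| 0.3 | 29% | 41% | 21% |
| 0.4 | 47% | 50% | 25% |
| 0.5 | 65% | 45% | 23% |

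With no difference between arms, a pattern of change in one arm but not the other would appear in 41-50% of trials. In half of those it would appear to favour the therapy, if the change is an improvement.

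**3. What baseline adjustment is worth.** Baseline is collected before allocation for every participant. Adjusting for it reduces the outcome SD by the factor √(1 − r²), where r is the baseline to follow-up correlation. The standardised effect becomes 0.80/√(1 − r²). The documents give no r, so a range is shown, with 24 per arm and two-sided 5%, and with the 0.80 taken in units of the unadjusted outcome SD:

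| Assumed r | √(1 − r²) | Effect in adjusted SD units | Power |
|---|---|---|---|
| 0 | 1.000 | 0.80 | 77% |
| 0.3 | 0.954 | 0.84 | 81% |
| 0.5 | 0.866 | 0.92 | 88% |
| 0.7 | 0.714 | 1.12 | 97% |

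The gain does not depend on baseline imbalance being seen.

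**The case against.** The strongest reply is that the protocol does not claim what the concern fears. It disclaims aiming at significance, calls the analyses mainly descriptive, names one primary measure and lists the between-group comparison before the within-group ones, which it adds for both arms. Nothing says that within-arm change will be read as a therapy effect, or that it will carry p-values. Such changes also help to judge whether the measures suit this population, which is part of objective (d). Model details and reporting conventions may stand in a fuller protocol or analysis plan that is not shown.

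Much of this stands, and it rules out two stronger readings.

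- **A reader might infer that any one of many results meets objective (a).** Five measures at two times give 10 between-arm and 20 within-arm comparisons. At 5% each, ten independent comparisons would give 1 − 0.95^10 = 40% chance of at least one false positive (about 17% if all were correlated at 0.8). But no passage says that a single result suffices. Ten of the 20 within-arm comparisons are in controls and cannot show benefit of the therapy, and hopefulness and quality of life are not literally named in objective (a). Those error rates describe a rule that the protocol does not contain.
- **A reader might infer that the 77% is wrong.** It is right for the contrast it describes. A lower figure follows only from splitting alpha, which neither the protocol nor the fix below does.

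What the reply does not answer is that the study is meant to show whether the therapy is likely to be effective and to supply an effect size. Descriptive or not, the text does not say whether that number is the one-week or eight-week result, adjusted or unadjusted, nor that within-arm change is excluded from it.

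**Conclusion.** The concern holds in a limited form. Within-arm comparisons with baseline are not evidence of a therapy effect and should not stand unlabelled beside the randomised comparison. The primary outcome needs one named time for objective (a) and the Phase III effect size, and baseline adjustment should be fixed rather than conditional.

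The 41-50% figure for one-arm-only significance rests on assumed equal change of 0.3 to 0.5 SD of change, 24 per arm and paired tests. It shows why the pattern misleads; it does not forecast this trial. The rise in power from 77% to about 81-97% rests on an assumed baseline correlation of 0.3 to 0.7.

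The stated power needs no correction. Formal multiplicity control is not required in a pilot of this kind. This is a worthwhile, cheap improvement to the stated analysis and does not undermine the design.

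**What to change.** In the quantitative analysis section, state that:

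1. Objective (a) and the Phase III effect size rest on one between-arm difference in the Patient Dignity Inventory at one named time, T2 or T3. The choice is the sponsor's and depends on whether early or lasting effect matters more.
2. That difference is always adjusted for the baseline Patient Dignity Inventory score and reported with a 95% CI.
3. The other time and the secondary measures are supporting estimates, each with a CI.
4. Within-arm mean change is shown descriptively, without p-values, and is not evidence of a therapy effect.

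Name the same time in the primary outcome and sample size sections. This costs a few sentences and needs no change to data collection or sample size. The one downside is that the time not chosen becomes secondary.
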